### Sample size justification

Approximately 6% of women will achieve smoking cessation with individual behavioural support via a structured intervention during pregnancy [10]. Previous large-scale trials in the UK have used a figure of 9% cessation in pregnancy unaided, with a further 6% cessation arising from an intervention [11]. Longitudinal data on pregnancy in women who quit after the first antenatal visit and before late pregnancy gives a similar figure (14.6%) [10]. We aim to double the ‘routine care’ cessation rate of 9% to give an intervention cessation rate of 18%. In terms of creating a model of care for pregnant smokers, we feel it is important to have a substantial increase in cessation rates over routine care to make it a viable clinic. Assuming a 5% level of statistical significance and 80% statistical power, the sample size is 225 per study arm. In a sensitivity analysis, under the assumption of no dropouts, the trial would have higher statistical power of precisely 90% or alternatively allow detection of a lower cessation rate of 16% in those randomised to the smoking cessation clinic.

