### Controls

The control group is 226 patients booked and recruited at the same time and randomised to ‘routine care.’ These patients have smoking cessation advice given as a ‘once-off’ at the booking visit via verbal or written information on the HSE Quit service, which is the current routine care in the Coombe and all obstetric units in Ireland [17]. The patients will attend either a general obstetric clinic or midwifery-led clinic and have a booking scan and 20–22-week anomaly scan as normal. The control group will be divided into two groups: 113 will have an additional scan at 32 and 36 weeks to screen for intrauterine growth restriction (IUGR), and 113 will receive no additional scans unless clinically indicated by their team. This is done to ensure testing of the hypothesis that the clinic as the intervention is responsible for any difference in outcomes, rather than the provision of additional ultrasound scans.

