## Analyses

### Statistical analysis

Outcomes in the smoking cessation intervention group will be compared to those for all control patients in an intention-to-treat analysis. A 5% level of significance will be used in a chi-square test for a difference in overall smoking cessation rates. Post hoc testing will consist of comparing the two control groups, i.e. controls under routine care versus controls with third trimester study scans (screening for IUGR). In a secondary analysis, IUGR rates will be compared between the smoking cessation group and the control group screened for IUGR. An analysis of covariance (ANCOVA) analysis will be used to adjust for the stratification factors (age, parity, and history of fetal growth restriction). Intervention adherence will be assessed, and the group comparisons will be reproduced in a per-protocol population. Potential patient selection bias will be assessed using the Berger-Exner test. Statistical analysis will be performed using the STATA IC15 statistical package.

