An anticipated challenge for this study is retention of participants in the clinical trial, as our previous work has shown a relatively high rate of non-attendance amongst smokers for antenatal clinic appointments [19]. Additionally, should a smoker develop certain complications (most commonly, diagnosis of gestational diabetes requiring metformin or insulin treatment), she will require transfer out to another specialist antenatal clinic, leading to drop out.

This study may lead to an improved model of care for women who smoke in pregnancy as well as recognition that this risk factor requires specialised antenatal input from healthcare professionals.

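### A per-protocol repeat based on intervention adherence would exclude women mainly from the STOP arm and so lean towards the clinic; a complier average causal effect would answer the same question with less bias

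*Protocol article*

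**What the plan says.** The main analysis, in the Statistical analysis section of the protocol article, is by intention to treat: "Outcomes in the smoking cessation intervention group will be compared to those for all control patients in an intention-to-treat analysis". The test is a chi-square at the 5% level. The section then adds: "Intervention adherence will be assessed, and the group comparisons will be reproduced in a per-protocol population". It gives no adherence threshold and no rule by arm.

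The two arms are asked to do different things. Under Smoking cessation program structure, STOP women see the practitioner 1 week, 4 weeks, 3 months and 6 months (or at the end of pregnancy) after a quit date. Of the controls, the Controls section says: "These patients have smoking cessation advice given as a ‘once-off’ at the booking visit via verbal or written information on the HSE Quit service". The same section assigns 113 of the 226 controls study scans at 32 and 36 weeks.

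On attendance, the Conclusions section warns that "our previous work has shown a relatively high rate of non-attendance amongst smokers for antenatal clinic appointments", without giving a rate. The primary outcome is validated continuous abstinence from the quit date to the end of pregnancy.

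**The concern.** Attendance is observed after randomisation and is likely to be related to the outcome. The practitioner schedule runs from the quit date, and abstinence is counted from the same date. A STOP woman who never sets a quit date cannot follow the schedule and cannot readily count as a quitter. A woman who relapses and stops coming is in a similar position. Excluding such women removes failures from the STOP arm. Controls with the same tendencies mostly stay in, because the cessation care they are due is complete at booking.

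The article presents the clinic as a model of care, so its effect in women who actually attend is a natural question for service planning. A direct per-protocol comparison would answer that question with a bias towards STOP. An adherence threshold in an analysis plan would not cure this, because the selection comes from comparing attenders in one arm with nearly unselected women in the other.

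**Working it through.** **Inputs.** From Sample size justification: 9% cessation under routine care, 18% planned in the STOP arm, 5% significance, 80% power and 225 per arm. From Controls: 226 controls. Assumed, because the article gives no figure: the fraction f of the STOP arm excluded, and the cessation rate among those excluded, written as r times the overall 9%. A two-sided test is also assumed.

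**The plan's own figure.** The article states: "Assuming a 5% level of statistical significance and 80% statistical power, the sample size is 225 per study arm". With the pooled-variance formula and no continuity correction:

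n = [1.960·√(2 × 0.135 × 0.865) + 0.842·√(0.09 × 0.91 + 0.18 × 0.82)]² / 0.09² = 225.1, rounded up to 226 per arm.

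Power at 225 per arm is 80.0%, so the stated size reproduces and 9% v 18% is a sound reference for the planned effect.

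**Per-protocol rate when the clinic has no effect.** True cessation is 9% in both arms, and exclusions are first taken from the STOP arm only:

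STOP per-protocol rate = 0.09 × (1 − f·r) / (1 − f)

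For example, f = 0.30 and r = 0 gives 0.09/0.70 = 12.9%. With r = 0.5 it is 0.09 × 0.85/0.70 = 10.9%. With r = 1 it stays at 9% for any f.

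The rejection rate of the two-sided 5% chi-square test (no continuity correction) was simulated with 20,000 replicates, 225 v 226 women randomised and all controls kept:

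| Excluded from STOP (f) | STOP rate, r = 0 | False positives, r = 0 | STOP rate, r = 0.5 | False positives, r = 0.5 |
|---|---|---|---|---|
| 10% | 10.0% | 6.5% | 9.5% | 5.5% |
| 20% | 11.3% | 12% | 10.1% | 7% |
| 30% | 12.9% | 23% | 10.9% | 10% |
| 40% | 15.0% | 43% | 12.0% | 16% |
| 50% | 18.0% | 66% | 13.5% | 26% |

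**When the bias reaches the planned size.** Setting the STOP rate to 18% gives f = 0.09/(0.18 − 0.09r). This is 50% if none of the excluded quit, and 67% if they quit at half the overall rate.

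**If controls are trimmed too.** Suppose a fraction g of controls is excluded, none of them quitters. The spurious difference is then 0.09/(1 − f) − 0.09/(1 − g):
- f = 30%: 2.9 points at g = 10%, 1.6 at g = 20%, and 0 at g = 30%.
- f = 50%: 8.0 points at g = 10%, 6.8 at g = 20%, and 5.1 at g = 30%.

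Trimming controls shrinks the bias, and equal trimming of equally selected women removes it.

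**The alternative estimator under the same null.** The complier average causal effect is the intention-to-treat risk difference divided by the difference between arms in the proportion exposed. With 9% in both arms the numerator is 0, so the estimate is centred on zero whatever the attendance.

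**The case against.** The strongest objection is that the article does not define the per-protocol set. Its definition is commonly left to the full protocol or the analysis plan, which are not shown. That stands: the missing definition is not criticised here, and a reader who infers that women would be excluded from the STOP arm only goes beyond the text. Controls could be excluded for missed study scans, crossover or transfer to another clinic, and the warning about non-attendance concerns smokers in general. The supportable word is mainly.

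A reader might also infer that the result is biased whatever definition is chosen. It is not. There is no bias when exclusion is unrelated to quitting, as might hold for eligibility errors or some transfers, or when both arms are trimmed alike.

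Nor do the documents support treating a spurious effect of the planned size as the expected result. It needs half of the STOP arm excluded with no quitter among them, and the article gives no attendance figure. Some of the text points the other way. Women stay in the STOP clinic whether or not they quit, and practitioner visits take place within the antenatal clinic, which the authors expect to help uptake.

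Finally, intention to treat remains the main analysis, and any claim that the per-protocol result would be the one quoted is speculation. What survives is narrower: the article commits to repeating the group comparisons in a per-protocol population alongside an assessment of intervention adherence, and an adherence-based version would select mainly within one arm.

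**Conclusion.** The point holds as a conditional one about a supporting analysis. If the per-protocol set rests on intervention adherence and non-attenders quit less often, the comparison is biased towards STOP. At 20-30% exclusion with no quitters among the excluded, the spurious gain is 2.3-3.9 points, against a planned difference of 9 points, with false-positive rates of 12-23%. If the excluded quit at half the overall rate, the gain is 1.1-1.9 points and the false-positive rate 7-10%. A spurious 18% v 9% is the extreme of the range shown.

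These figures rest on assumed exclusion fractions, assumed cessation among the excluded, a two-sided test and no exclusions among controls; exclusions of non-quitting controls would lower them. The primary intention-to-treat conclusion is not affected. The change is worth making, but it is not a threat to the trial.

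**What to change.** Replace the per-protocol comparison with a complier average causal effect for cessation that keeps all women as randomised. If the per-protocol comparison is kept, label it descriptive and report the complier estimate beside it.

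- **Instrument:** randomised allocation.
- **Exposure:** any attendance at the STOP clinic or its cessation programme, fixed before analysis. A high attendance cut-off should be avoided. Women below it would still receive part of the care, so allocation would act by a route other than the defined exposure, and a real effect per attender would be overstated.
- **Estimation:** two-stage instrumental-variable estimation with its confidence interval, using exposure as recorded in both arms. No passage says that controls cannot enter the clinic, and the article itself expects crossovers, so zero control exposure should not be assumed.
- **Reporting:** give attendance by arm as a description of exposure, and state the assumption that allocation affects cessation only through attendance.

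The cost is a few sentences of analysis wording. Adherence is already to be assessed, so little or no new data should be needed beyond a record of any control who attends the clinic. The price is a wider interval and reliance on the exclusion restriction, which the data cannot verify.

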### Primary outcome

The Russell Standard for reporting of smoking cessation in clinical trials will be followed [16].

The primary outcome is self-reported, continuous abstinence from smoking between the quit date and end of pregnancy, validated by exhaled CO or urinary cotinine. The quit date is targeted as being at or before 16 weeks’ gestation and no further than 28 weeks’ gestation.

Secondary outcomes are (see Additional file 1):
*Smoking*. Number of cigarettes smoked. Smoking cessation at 3 months post quit date, 6 months post quit date and/or end of pregnancy. Smoking cessation at 6 months postpartum*Psychological*. Urge to smoke, tobacco withdrawal symptoms, self-confidence in stopping smoking, self-reported depression at end of pregnancy*Fetal morbidity and mortality including neonatal measures*. Miscarriage, stillbirth, neonatal death, birth weight, estimated fetal weight at 32 weeks, estimated fetal weight at 36 weeks, spontaneous pre-term birth, iatrogenic pre-term birth, birth injury, neonatal complication, oxygen dependence, admission to neonatal unit, length of stay of neonate. Modified from Core Outcome Measures in Effectiveness Trials (COMET) Initiative [18]*Maternal morbidity and mortality including delivery outcomes*. Maternal death, mode of delivery, need for induction/delivery, maternal need for intensive care, maternal length of stay, pre-eclampsia, pregnancy-induced hypertension, postpartum haemorrhage, blood transfusion, late maternal complication. Modified from COMET Initiative [18]*Qualitative measures*. Satisfaction with the results of care, confidence as an active participant in healthcare decisions, confidence in healthcare providers.

The secondary outcomes are defined in detail in Additional file 1.

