#### Ultrasound

An ultrasound scan is performed at booking (early second trimester) and between 20 and 22 weeks for anomaly screening. Additional growth scans are carried out at 32 and 36 weeks to screen for fetal growth restriction. Triplicate measures of biparietal diameter, head circumference, abdominal circumference, and femur length are obtained, and an estimate of fetal weight is calculated using the Hadlock formula [13]. Fetal adiposity is measured at the fetal thigh and abdomen as described previously [14]. Doppler measurements are obtained from both the umbilical and middle cerebral arteries. At the time of these growth scans, the self-reported number of cigarettes is recorded along with the timing of the last cigarette use. Exhaled carbon monoxide (CO) and urinary cotinine are measured. Images taken by the ultrasonographer are qualitatively controlled and scored according to the scheme described by Salomon et al. [15].

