#### Smoking cessation program structure

A smoking cessation practitioner assesses the patient as part of the primary care giving team and measures exhaled CO. The Health Service Executive (HSE) Tobacco Cessation Support Program is a structured behavioural support program used by smoking cessation specialists in Ireland. It uses behavioural change techniques to support the tobacco user through the process of quitting by increasing confidence and motivation to quit and developing personal coping skills to sustain the quit attempt over time. Once the smoking cessation intervention is performed, a ‘quit date’ is set. The smoking cessation practitioner then sees the patient according to the following schedule:
One week post quit dateFour weeks post quit dateThree months post quit dateSix months post quit date/end of pregnancy (depending on gestation).

If a patient is still smoking at 4 weeks post quit date, NRT is offered in accordance with HSE guidelines which recommend its use in pregnancy only after a psychological intervention has failed.

The smoking cessation practitioner return visits are held in the clinic alongside the antenatal team. Current smoking status is recorded at each visit to the smoking cessation practitioner. If the patient has quit smoking, the timing of cessation and any aids used are recorded. Measures of urge to smoke, tobacco withdrawal score, and confidence in quitting are recorded. Quantitative measurement of urine cotinine is performed at 32 and 36 weeks, coinciding with the third trimester ultrasound scans. The HSE-adapted Russell Standard definitions of Quit are used [16]:
*Self-reported Quit*. This is defined as a self-report of smoking not more than five cigarettes from the quit date. A standard abstinence question is ‘Have you smoked at all since (date of start of abstinence period) A: No, not a puff; B: 1–5 cigarettes; C: More than 5 cigarettes?’ Answer A or B can be classified as a Self-reported Quit.*Validated Quit*. A Self-reported Quit that is validated with a CO monitor reading of less than 10 ppm is classified as a Validated Quit.

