### Postnatal assessment and qualitative measures

After delivery, a member of the research team meets the patient to perform a CO test. A pseudonymised questionnaire is provided to record her current smoking habits, information on cessation (if it has occurred), and any aids used. Satisfaction with care, confidence in healthcare providers, and confidence as an active participant in healthcare decisions are recorded with Likert-type scales. An Edinburgh Postnatal Depression Scale score is also recorded.

A final cessation check is performed at 6 months postnatal to screen for recidivism and is validated by a CO measurement, in line with the Russell Standard for reporting in smoking cessation clinical trials [16].

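### The primary outcome's CO-or-cotinine rule conflicts with the CO-only Validated Quit definition, and on the text shown the tests it can draw on differ by allocated group

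*Protocol article*

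**What the plan says.** The Primary outcome section defines continuous abstinence from the quit date to the end of pregnancy, self-reported and "validated by exhaled CO or urinary cotinine". It adds: "The Russell Standard for reporting of smoking cessation in clinical trials will be followed".

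The section Smoking cessation program structure, citing the same reference, gives a different rule: "A Self-reported Quit that is validated with a CO monitor reading of less than 10 ppm is classified as a Validated Quit". It has no cotinine route and no cotinine cut-off.

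The test schedule has to be pieced together from several sections:

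- Ultrasound, on the 32- and 36-week growth scans: "Exhaled carbon monoxide (CO) and urinary cotinine are measured".
- Smoking cessation program structure: "Quantitative measurement of urine cotinine is performed at 32 and 36 weeks, coinciding with the third trimester ultrasound scans". The practitioner also measures CO and sees STOP women at 1 week, 4 weeks, 3 months and 6 months (or end of pregnancy) after the quit date.
- Controls: 113 women have the 32- and 36-week scans and "113 will receive no additional scans unless clinically indicated by their team". Smoking advice is given once, at booking.
- Postnatal assessment: "After delivery, a member of the research team meets the patient to perform a CO test". This section is not limited to the STOP arm.

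Statistical analysis compares STOP with all controls pooled, by intention to treat, using a chi-square test at 5%.

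**The concern.** There are two linked problems in the definition of the primary endpoint.

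First, the two sections do not give the same rule. The article shows no deciding test, no deciding occasion and no treatment of discordant results.

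Second, the occasions on which CO or cotinine could be taken follow allocation. With an open *or*, a woman who has more occasions is less likely to lose a true quit because she missed a test. If she has misreported, she also has more chances to pass. The protocol itself expects relatively high non-attendance among smokers (Conclusions), so missed tests are a realistic route. The trial cannot blind women or clinicians, and analysis by study number does not remove a difference in how often women are tested. A difference in verification would enter the primary chi-square test directly.

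**Working it through.** **1. The two definitions side by side**

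| CO | Cotinine | Validated Quit (programme section) | Primary outcome section |
|---|---|---|---|
| below 10 ppm | negative | validated | validated |
| 10 ppm or more | negative | not validated | validated, reading *or* literally |
| below 10 ppm | positive | validated | no rule shown |
| 10 ppm or more | positive | not validated | not validated |

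The second row is the direct conflict. The third is an open question. The article does not say how often either would occur.

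**2. Test occasions on the text shown**

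| Group | Practitioner CO | CO and cotinine at 32 and 36 weeks | Post-delivery CO |
|---|---|---|---|
| STOP | yes | yes | yes |
| Scanned controls (113) | none described | probably (tied to the growth scans; not restated under Controls) | yes |
| Unscanned controls (113) | none described | none described | yes |

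**3. Effect if any one passing test suffices**

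Inputs from the protocol: 9% routine-care cessation; 225 per arm (Sample size justification); controls 113 + 113 (Controls). The plan's sample size reproduces: 9% against 18%, two-sided 5% and 80% power give 225.1 per arm by the pooled-variance formula.

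Assumptions not in the protocol:
- no true effect, with true quits T = 9% or 12% in every group;
- no misreporting;
- each occasion attended independently with probability a;
- no test attended means not verified;
- three occasions (32 weeks, 36 weeks, post-delivery) for STOP and scanned controls, one for unscanned controls.

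Formulas: three occasions, v3 = T[1 − (1 − a)³]; one occasion, v1 = T·a; pooled controls, (v3 + v1)/2. For example, with T = 9% and a = 0.8: v3 = 0.09 × (1 − 0.008) = 8.93%; v1 = 0.09 × 0.8 = 7.20%; pooled controls 8.06%; difference 0.86 points.

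The false-benefit rate is the exact binomial probability that the pooled two-proportion z-test (equivalent to the chi-square) exceeds +1.96 with 225 against 113 + 113.

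| T | a | STOP | Unscanned controls | STOP minus pooled controls | False STOP benefit (nominal 2.5%) |
|---|---|---|---|---|---|
| 9% | 0.70 | 8.76% | 6.30% | 1.2 points | 6.7% |
| 9% | 0.80 | 8.93% | 7.20% | 0.9 | 5.0% |
| 9% | 0.90 | 8.99% | 8.10% | 0.4 | 3.5% |
| 9% | 0.95 | 9.00% | 8.55% | 0.2 | 2.9% |
| 12% | 0.70 | 11.68% | 8.40% | 1.6 | 7.8% |
| 12% | 0.80 | 11.90% | 9.60% | 1.2 | 5.6% |
| 12% | 0.90 | 11.99% | 10.80% | 0.6 | 3.8% |
| 12% | 0.95 | 12.00% | 11.40% | 0.3 | 3.1% |

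The range is about 3–8%. Counting both tails, T = 12% with a = 0.8 gives 5.6% + 0.9%, about 6.6% against 5%. The practitioner CO tests are left out; for true quitters they could add at most T − v3, about 0.3 points.

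**4. Effect if every test done must pass**

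Add false claimants F, each passing a test with probability q (assumed). The verified rate with k occasions is T[1 − (1 − a)^k] + F[(1 − a + aq)^k − (1 − a)^k]. With T = 9%, F = 6%, a = 0.95 and q = 0.4: three occasions give 9.5%, one gives 10.8%, pooled controls 10.2%. STOP is now 0.7 points lower with no true effect, so the sign depends on a rule the article does not state.

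**5. One common test**

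With the same test and occasion for every woman, and equal attendance, verified rates are equal under no effect and the two-sided error is 5.0%. The sample size does not change.

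**The case against.** The strongest reply is that the any-one-pass rule is a reading, not the protocol's statement. The endpoint runs to the end of pregnancy, so a 32-week test or an early practitioner CO cannot by itself confirm abstinence to delivery. If the post-delivery CO decides, the difference in opportunity disappears. That is right, and it is why the effect is stated conditionally. But the Primary outcome section does not name that test, and it admits cotinine, which the article places only at 32 and 36 weeks.

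Fig. 3 and Additional file 1 are not shown and may give a test schedule for controls. That could reduce the second problem. It would not align the two definitions.

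The Validated Quit sits in the intervention section and is described as an HSE adaptation, so it may be meant as a programme definition. Both sections still cite the same standard, and the primary outcome is said to follow it.

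The inflation depends on the inputs. At T = 12% and a = 0.8, a within-woman attendance correlation of 0.5 lowers the false-benefit rate to 4.1%, and 0.8 lowers it to 3.1%. Higher attendance at the post-delivery visit would also reduce it.

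A reader might infer three stronger things that the article does not support:
- **That the rule favours STOP.** The direction depends on the unstated rule.
- **That a passing CO overrides a positive cotinine.** No rule for discordant results is shown.
- **That error rates reach 10–20%.** At a = 0.8 and 0.7 the false-benefit rate would be 9.7% and 16.3% (T = 9%), or 11.8% and 20.7% (T = 12%). Those figures need scanned controls to lack the tests that the Ultrasound section places at the growth scans.

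**Conclusion.** The conflict between the two definitions stands on the text. On what is shown, the opportunity for verification also depends on allocated group, so an *or* rule applied as written can produce different verified rates with no true effect.

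The size is modest: 0.2 to 1.6 points between STOP and pooled controls, against a planned difference of 9 points, and a false-benefit rate of about 3–8% instead of 2.5%. This rests on 9–12% true quits, independent attendance of 70–95%, no misreporting, half the controls with one occasion against three, and any one pass sufficing. Under an all-must-pass rule the bias can reverse, and under a common post-delivery test it is absent.

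This should be fixed because it concerns the primary endpoint and costs little. It does not show that the trial's result will be biased towards STOP.

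**What to change.** - Define the primary outcome as self-reported continuous abstinence plus one validation at one time point scheduled for all three groups: the existing post-delivery CO, below 10 ppm. Count a missing CO as smoking.
- Align the Primary outcome section with the Validated Quit definition by removing cotinine as an alternative route in the primary rule.
- Report the 32- and 36-week CO and cotinine as supportive or sensitivity analyses in the groups that have them, and state under Controls whether scanned controls are tested at those scans. Identify NRT and e-cigarette users: NRT is offered within the STOP schedule, and a nicotine product may itself affect cotinine (general pharmacology, not stated in the article).

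The cost is a wording change in an ongoing trial, with no extra tests and no change in sample size. The real downside is that a single CO reading covers a short exposure window, and cotinine no longer contributes to the primary result. That limitation applies equally in every group.
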